## 4 STUDY DESIGN

This study will be a double-blind Phase II clinical trial conducted in three Stages (A, B, and C). Antigens are coded, and subjects are randomly assigned a template for placement of skin test antigens. Stage A will provide an initial indication of the safety of the two new test antigens in ten healthy members of this leprosy endemic population (five subjects per antigen at two dosages each). Stage B will expand this analysis by an additional 90 healthy subjects (45 subjects per antigen). If any of the subjects in Stage A or B show ulcerations at the 1.0 $\mu$ g dose of MLSA-LAM or MLCwA test sites, then only the 0.1 $\mu$ g dose will be used for Stage C. The final stage, Stage C, is divided into two parts. The first part, Stage C-1, will assess the safety of both antigens at the high dose (1.0 $\mu$ g) in populations at a higher risk of developing ulcerations at the skin test site. A total of eighty subjects will be recruited: 20 household contacts of BL/LL leprosy patients, 20 BL/LL leprosy patients, 20 BT/TT leprosy patients, and 20 TB patients. The second part, Stage C-1b, is a continuation of Stage C-1 with the same number of subjects recruited from the same groups to assess the reactivity of both antigens at the low dose (0.1  $\mu$ g). Safety data will be collected following each stage and reviewed by the SMC. A report will be forwarded to DMID, NHRC, and CSU IRB for review and approval.

This study will define a positive skin test reaction for MLSA-LAM and MLCwA and this definition will be used in estimating sensitivity and specificity for each skin test antigen and dosage. The skin test reactions (as compared to reactions from tuberculin/PPD, and Phase I studies of MLSA-LAM and MLCwA) will vary among the groups participating in this study. It is expected that the BT/TT leprosy patients and healthy contacts of leprosy patients will have larger indurations at both *M. leprae*-derived antigen sites, and a variable reaction at the site of the tuberculin/PPD. The non-contacts, BL/LL leprosy patients, and tuberculosis patients will have smaller indurations at all leprosy skin test sites, and a variable reaction at the site of tuberculin/PPD. Finally, the tuberculosis patients will react with a large induration at the tuberculin/PPD site.

### 4.1 Rationale for Design Features

The rationale behind this study design is to ensure the safety of each antigen at both dosages in a low risk population (non-contacts, who are healthy individuals without known exposure to leprosy), before moving to a higher risk population (contacts of leprosy patients, clinical leprosy patients, and tuberculosis patients). Tuberculin/PPD will be used as a control to measure reactivity of not only BCG vaccination, but also tuberculosis exposure, and exposure to non-pathogenic environmental mycobacteria to some extent. In all subjects, we will be comparing diameters of the erythema and induration reactions to tuberculin/PPD with those to the new leprosy skin test antigens. Reactogenicity of antigens (or lack thereof) in non-contacts will establish the baseline reaction and aid in establishing a “cut off” point to define a “positive” skin test. Saline will serve as a diluent control in Stage A and B only. Specificity and sensitivity will be determined for each antigen and dosage.

## 4.2 Description of Study Groups

| Stage | Study group                                                                                                                      | Number of groups | Sample size/group | Total sample size | No. injection sites | Estimated completion time |
|-------|----------------------------------------------------------------------------------------------------------------------------------|------------------|-------------------|-------------------|---------------------|---------------------------|
| A     | Non-contacts                                                                                                                     | 2                | 5                 | 10                | 4                   | 1 month                   |
| B     | Non-contacts                                                                                                                     | 2                | 45                | 90                | 4                   | 3 months                  |
| C-1   | Contacts (co inhabitants) of BL/LL leprosy patients
BL/LL leprosy patients
BT/TT leprosy patients
Tuberculosis patients | 4                | 20                | 80                | 3                   | 3 months                  |
| C-1b  | Contacts (co-inhabitants) of BL/LL leprosy patients
BL/LL leprosy patients
BT/TT leprosy patients
Tuberculosis patients | 4                | 20                | 80                | 3                   | 3 months                  |

## 4.3 Approximate Time to Complete Study Enrollment

The total estimated time to complete the protocol is 17 months, however, this is not a continuum, because safety data will be collected after each stage of the study (A, B, C-1, and C-1b), reviewed by the SMC, and the resultant SMC report will be forwarded to DMID, NHRC, and CSU IRB for approval. Estimated time for this review and approval process is 4 months (minimum) per stage, resulting in an additional 16 months. Thus, the total estimated time to complete all stages of this Phase II Clinical Trial is 33 months (or 2.75 years).

## 4.4 Sequence and Expected Duration of Subject Participation

Subject participation for each stage of the trial will be 7 days ( $\pm 1$  day). If induration  $> 10$ mm at any injection site is observed during the first 7 days, involvement in the study will last for 28 days ( $\pm 3$  days) or until all reactions are resolved or stabilized. Total time involvement for each participant is approximately 5.0 hours, as follows:

| Trial Period  | Description                                              | Stage |   |     |     |  | Est.
Duration
(hours) |
|---------------|----------------------------------------------------------|-------|---|-----|-----|--|-----------------------------|
|               |                                                          | A     | B | C1a | C1b |  |                             |
| Day –10 to –1 | Description of the study to allow informed consent       | X     | X | X   | X   |  | 1.00                        |
| Day 0         | Informed consent process                                 | X     | X | X   | X   |  | 0.50                        |
|               | Screening:                                               | X     | X | X   | X   |  | 1.50                        |
|               | Health Questionnaire/History Form                        |       |   |     |     |  |                             |
|               | Physical Examination                                     |       |   |     |     |  |                             |
|               | Eligibility Checklist/Enrollment                         | X     | X | X   | X   |  | 0.25                        |
|               | Blood Sampling                                           |       |   | X   | X   |  | 0.25                        |
| Day 0         | Administration of antigen                                | X     | X | X   | X   |  | 0.25                        |
|               | Reaction recorded ~15min and 30 min (for stage C1b only) |       |   |     |     |  | 0.25                        |
| Day 2         | Reading skin tests                                       | X     |   |     |     |  | 0.25                        |
| Day 3         | Reading skin tests                                       | X     | X | X   | X   |  | 0.25                        |
| Day 7         | Reading skin tests                                       |       | X | X   | X   |  | 0.25                        |
|               |                                                          |       |   |     |     |  |                             |
| Day 28        | Reading of positive reactors                             | X     | X | X   | X   |  | 0.25                        |
| Total Time    |                                                          |       |   |     |     |  |                             |
|               | Study participants                                       |       |   |     |     |  | 5.0                         |

## 4.5 Methods for Collecting Data for Assessment of Study Objectives

Administration of antigens and reading of induration will normally be performed by separate teams, although it will be acceptable for an administrator to also be a reader of the same subject. Administrators and readers will be blinded to the antigen identity at each site. Each antigen site will be read and recorded by two independent readers at ~15 min, 45-51 h and 69-75 h for Stage A, and ~15 min, 69-75 h, and 6-8 days for Stage B, ~15 min, ~30 min (for stage C1b only), 2-4 days, and 6-8 days for Stage C. The method for reading will be as follows: The site will be gently palpated, the limits of the induration determined with the fingers, and the largest transverse diameter will be measured with a soft, flexible, transparent ruler by two independent readers. The maximal diameter will be recorded by each reader, and an average of the two will be used. Readings from both readers will be analyzed for correlation (the most experienced administrator/reader will be used as the 'gold standard'). In the case that there are systematic reading errors on the part of the second reader, the reader will be given more supervision. In the case that the second reader shows 'terminal digit preference' in his/her readings (i.e., his/her readings always end in an even or odd number), further training will be given without explaining to the reader the reason for the additional training, in order to avoid correcting one bias by potentially introducing another [adapted from "Guidelines for Conducting Skin Test Surveys in High Prevalence Countries," issued by the International Union Against Tuberculosis and Lung Disease (24)]. Erythema will also be measured (by ruler) and recorded at each time point.

Any subject with an induration greater than 10 mm at either the 45-51 h or 69-75 h reading for Stage A, and 69-75 h or 6-8 day readings for Stage B, and 2-4 day or 6-8 day readings for Stage C, will be asked to return at 25-31 days for follow-up. Those subjects who need to return at day 25-31 will have their study/subject number posted on the bulletin board of the appropriate college/campus (primarily healthy non-contacts in all stages) and/or will be given instructions and a card indicating the date of their next visit (primarily patients and contacts of leprosy patients in Stage C) to serve as a reminder, without revealing the identity of the subject. Subjects experiencing any persistent reaction or adverse event will be followed until the resolution or stabilization of symptoms. Adverse events will be graded and recorded in the CRFs during each study visit.

Prior to study enrollment, all participants will have provided informed consent after having been told about the study and what is expected for participation. Source documents pertaining to individual study subjects will include the Skin Test Reading forms and Case Report Forms (CRFs) as follows:

- Eligibility Checklist
- Informed Consent Form
- Demographics/Medical History Form
- Antigen Administration Form
- Follow-up Examination and Reaction Form
- Skin Test Reading Forms for each time point
- Study Termination Form
- Adverse Event Form
- Serious Adverse Event Form

Most data on the CRF will be obtained directly from the participant. Some clinical data relating to the treatment history of the participant for tuberculosis (TB) or leprosy as applicable, will be confirmed from their medical records following completion of a separate Informed Consent Document. Only the information specified in the CRF will be derived from these records. Data from the CRFs and Skin Test Reading forms will be entered into electronic files at AH, and sent monthly via Compact Disk (CD) to the Data Control Center (DCC), EMMES Corporation, where the data will be analyzed by uploading onto the EMMES computer database. As a quality control measure, the data will be checked for anomalies and inconsistencies through The EMMES Corporation's Data Integrity Evaluation System. The Data Manager will send a Data Resolution Form (DRF) outlining missing values, out-of-range values, and other data anomalies to the central clinical site for reconciliation of data discrepancies.

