At the end of each training day, each skin test administrator will be given the opportunity to administer an actual tuberculin/PPD skin test with Tubersol® (Aventis Pasteur Inc., Swiftwater, PA) in training for Stages A, B and C-1 or RT 23 SSI (Statens Serum Institute, Copenhagen, Denmark) for Stage C-1b to at least three consenting volunteer leprosy health workers at Anandaban. The trainee's skin test administration technique will be observed and checked by the trainer using a procedural checklist. Seventy-two hours later, the trainees will record the readings from all of the volunteer leprosy health workers who had received tuberculin/PPD. Every trainee will read each reaction several times and the results will be recorded so that the reader's consistency can be assessed. The trainer will also read each of the volunteers' skin test reactions. Variation from the trainer's readings will be plotted on a standard correlation table, as recommended by the International Union against Tuberculosis and Lung Disease. The correlation chart will be used to identify systematic variations between the trainee's and the trainer's readings. Variations from the trainer's readings should not exceed 1 mm. Trainees whose skin test readings vary from the trainer's on average more than 2 mm will not be invited to participate in the study.

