### 13.4 Study Outcome Measures

The primary outcome measure of this study is induration resulting from the skin test antigen DTH response. The method for measuring induration has been described in Section 4.5, "Methods for Collecting Data for Assessment of Study Objectives". As mentioned previously, evaluation of this observation variable will be performed using the same techniques used to evaluate the tuberculin/PPD response. A tuberculin reaction greater than 10mm of induration is classified as positive for persons who are not immunocompromised or previously in contact with TB patients, but have other risk factors for TB, such as living in a country where TB is prevalent. Induration measurements will be taken on days 2 and 3 (Stage A) and days 3 and 7 (Stage B and C) after skin test administration, at each test antigen site. If a subject is observed to have an induration greater than 10 mm at any injection site, at either study visit, they will

be asked to return at 25-31 days for a final induration measurement. Any reaction that persists will be followed-up until resolved or stabilized.

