### 13.6 Sample Size Considerations

The primary variable outcome measure used for all calculations will be the mean induration measurement obtained from two independent readers for each skin test site. Our experience in this region of Nepal suggests that no more than 10% of subjects will be lost to follow-up. We are not planning to administer skin tests to additional subjects should some of the subjects not return for the 45-51 hour or later readings.

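### The digit-preference trigger in Section 4.5 requires readings that are always even or always odd and covers only the second reader, so it cannot catch rounding to 5 mm and rarely catches partial preference

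*Protocol*

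**What the plan says.** Section 4.5 has two readers measure every site. "The maximal diameter will be recorded by each reader, and an average of the two will be used". Section 13.6 names as the variable for all calculations "the mean induration measurement obtained from two independent readers for each skin test site", and Section 13.4 states: "The primary outcome measure of this study is induration resulting from the skin test antigen DTH response".

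The in-study reader checks are all in Section 4.5:

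- Agreement: "Readings from both readers will be analyzed for correlation", with the most experienced reader as the reference. Systematic errors by the second reader lead to closer supervision.
- Digits: "In the case that the second reader shows 'terminal digit preference' in his/her readings", further training follows without the reason being given. An i.e. clause defines the preference as "his/her readings always end in an even or odd number".

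Before the study, Section 9.3.1 sets a target of no more than 1 mm deviation from the trainer and adds an exclusion: "Trainees whose skin test readings vary from the trainer's on average more than 2 mm will not be invited to participate in the study". Neither limit concerns last digits.

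**The concern.** The rule names a known fault in skin-test reading but defines it so narrowly that common forms escape. Rounding to 5, 10, 15 and 20 mm mixes odd and even endings. A strong but incomplete even preference is cleared by one odd reading. A 0 mm reading counts as even, so one negative site clears a reader who otherwise records only odd numbers, while a reader who sees only negative sites meets the definition without any bias. Sections 8.2.2 and 13.2 expect small or no indurations at the leprosy antigen sites in BL/LL and TB patients, so zeros are likely in the stage that remains.

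The reference reader supplies half of every averaged value and has no stated digit check. At stake is the induration distribution. Section 13.5 will look for bimodality in it, Section 13.9.3 will derive cut-offs from it, and the working limit of 10 mm lies on a multiple of 5. Heaping there can create false modes and coarsen the available cut-offs.

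**Working it through.** The protocol gives no sample size or threshold for this check, so there is no figure to reproduce.

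**Inputs from the protocol.** The definition, the restriction to the second reader and the averaging (4.5); a pool of four to six administrators/readers (9.3.1); 80 subjects in C-1b (13.7), three sites each (4.2) and two scheduled delayed readings. That gives 80 × 3 × 2 = 480 site-readings per reader position, or 960 over both positions. Shared equally, which is an assumption, this is 960/6 = 160 to 960/4 = 240 per person. The actual number is not stated.

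**Step 1: chance of a flag.** With p the share of even readings and n the readings judged, P(flag) = pⁿ + (1 − p)ⁿ.

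| Share even | n = 30 | n = 60 | n = 120 |
|---|---|---|---|
| 80% | 0.1% | about 0 | about 0 |
| 90% | 4.2% | 0.2% | about 0 |
| 95% | 21% | 4.6% | 0.2% |
| 99% | 74% | 55% | 30% |

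For a reader who rounds to 0 and 5 in equal mix, P(flag) = 2 × 0.5ⁿ, which is 0.002 at n = 10 and 2 × 10⁻⁹ at n = 30. It is exactly zero once one 0 and one 5 have been recorded.

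**Step 2: zeros.** If 80% of sites read 0 mm (assumed), an unbiased reader's even share is 0.8 + 0.2/2 = 0.9.

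**Step 3: do the other checks catch rounding to 5 mm?** Whole-millimetre values deviate from the nearest multiple of 5 by 0, 1, 2, 2 and 1 mm. The mean is 6/5 = 1.2 mm, under the 2 mm exclusion limit, although 2 in 5 readings (40%) miss the 1 mm target. For an assumed mean of 12 mm, correlation with the unrounded reading stays at 0.905, 0.962 or 0.984 for SD 3, 5 or 8 mm, with bias near zero.

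**Step 4: effect on the averaged outcome.** Simulation with assumed true induration of mean 12 mm, SD 4 mm, and independent reader error of SD 1 mm:

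| Reading behaviour | Average > 10 mm | Average exactly 10 mm |
|---|---|---|
| Both honest, whole mm | 67% | 4% |
| One rounds everything to 5 mm | 65% | 8% |
| Both round half their readings | 62% | 13% |
| Both round everything | 51% | 33% |

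Error-free continuous induration gives 69% above 10 mm. The fair comparator is 67%, because whole-millimetre recording alone accounts for the difference.

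**The case against.** The sentence is a retraining trigger. It excludes no data and enters no estimate, and a supervisor who notices 5, 10, 15, 10 may act under the separate provision for systematic errors. Trainees' deviations from the trainer are plotted before the study, the data centre looks for anomalies, and a Manual of Operations that is not shown may say more. Nothing in the protocol suggests that these readers round. The 10 mm limit is provisional, and the final cut-off will be derived from the data.

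Most of this stands, and it limits the size of the point. It does not remove the point: the definition is introduced by i.e., no other section states a digit check, and the training and correlation checks can pass a reader who rounds to 5 mm.

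Three stronger readings are tempting, and the documents support none of them:

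- A reader might infer an error of about 18 points in the primary outcome (51% against 69%). That needs both readers to round every reading, under assumed inputs, and uses the wrong comparator. The direction also depends on the strict inequality: with at least 10 mm as the limit, full rounding by both gives 83% against 71%.
- A reader might infer that nearly all partial preference is missed. At 99% even, the rule flags 74% of readers after 30 readings, and the number of readings per person is not given.
- A reader might infer that the check would certify the data as clean. Section 4.5 describes no such report.

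**Conclusion.** The point holds as a minor defect in a quality-control rule. As written, the trigger cannot flag rounding to 0 and 5 once both digits have occurred. It seldom flags even shares of up to 90% from 30 readings, or up to 95% from 60. It is distorted by 0 mm readings and leaves the reference reader without a digit check.

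Harm to the outcome depends on behaviour that the protocol neither documents nor rules out. Under the stated assumptions, averaging confines the loss to about 2 points when one reader rounds everything (67% to 65%). The loss is about 5 points when both round half their readings and 16 when both round everything. The concern is therefore mainly that both readers might heap, which is why the unchecked reference reader matters. Section 13.7 says Stages A, B and C-1 were completed before this amendment, so retraining can act only in C-1b.

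**What to change.** Replace the always-even-or-odd definition in Section 4.5. For every reader, including the reference reader, tabulate the last digits of non-zero readings at each monthly data transfer. Trigger the unexplained retraining already planned when the share ending in 0 or 5, or the share ending in even digits, is clearly excessive by a preset, strict threshold applied to cumulative readings, so that repeated monthly looks do not multiply false flags. Judge each reader against the other readers of the same sites. A fixed 20% for 0 and 5 is unsafe because the expected share depends on the induration distribution: for readings around 5 mm with SD 1.5 mm (assumed), an unbiased reader has about 26%. Because such a comparison cannot show heaping that both readers share, also inspect the pooled table for peaks at 5 and 10 mm.

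For Stages A, B and C-1, produce the same table before the cut-off is chosen. It can show whether heaping is present but cannot undo it.

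The cost is one table per reader from data already sent to the data centre, and an occasional unneeded retraining session.

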## 4.6 Covariates

In addition to the primary and secondary outcome measures described above, potential confounding factors will be evaluated, as follows:

- Healthy non-contacts: Age, sex, BCG status, and tuberculin/PPD reaction

- Contacts of leprosy patients: Age, sex, BCG status, type of contact, length of contact, characteristics of index case, and tuberculin/PPD reaction
- Leprosy patients: Age, sex, BCG status, type of leprosy, smear result, length of treatment, history of reaction, and tuberculin/PPD reaction
- TB patients: Age, sex, BCG status, length of treatment, and tuberculin/PPD reaction

First, the influence of these confounders on induration size and proportion positive will be evaluated at a univariate setting. Factors found to be significant at univariate level will be entered into the multivariate model. These analyses will not only be used to test the differences between groups, but will also allow us to estimate the adjusted geometric mean reaction size for each group (after transformation to the natural reaction size). The multivariate logistic regression model for “positive reaction” outcome will also allow us to obtain sensitivity and specificity, both adjusted for important confounding factors.

